#### 2.10.4. Premature Termination of the Study

The study can be terminated prematurely if the number of SAEs or the rate of vascular calcification is significantly higher in the treatment group *versus* the placebo group.

The study will be terminated if a causal relation between MK-7 treatment and the adverse events or progression of vascular calcification is highly suspected. If the study is terminated prematurely, all subjects will be informed about their results and the reason why the study is terminated.

#### 2.10.5. Withdrawal of Individual Subjects

Subjects can leave the study at any time for any reason if they wish to do so, without any consequences. The investigator can decide to withdraw a subject from the study for urgent medical reasons or in case of demonstrable poor adherence to the study medication. This is assessed by interview and pill-count. If subjects are required to take vitamin-K antagonists (coumarins) during the course of the study (for example due to Deep-Venous Thrombosis or Pulmonary Embolism) they will be withdrawn from the study.

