### 2.8. Statistical Analysis

The main outcome parameters (CAC-score) and CAC-score progression will be presented as continuous variables. In addition, the amount of CAC-score progression (in both Agatston-score and Mass-score) will be dichotomized (rapid progression and slow progression) using a cut-off of an annual progression of 15% [33].

Data will be analyzed based on the intention-to-treat principle. To adjust for potential confounders (age, gender, BMI, blood-pressure, smoking, cholesterol, glucose and medication use), multiple analysis of variance will be performed. For continuous variables, multivariable linear regression will be applied. For longitudinal data analysis (*i.e.*, progression between baseline, 12 months, and 24 months of follow-up) Generalized Estimating Equations (GEE) analysis will be applied to adjust for multiple testing. Additional statistical analyses will be performed as appropriate (e.g., Hazzard ratio calculation). All statistical analysis will be performed using the statistical package SPSS 22 (IBM Corp, Armonk, New York, USA). The statistical tests will be performed using a two-sided significance level of 5%.

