### 2.9. Sample Size

The mean annual CAC-progression reported in literature ranges from 24% to 51% and has a large inter-individual variation depending on many factors such as the baseline CAC-score, medical history, medication-use, body-mass index, scanner type and manufacturer. The standard deviation in CAC-score progression in a population comparable to our intended population is reported to range from 21% to 36% [33]. Since we use strict inclusion and exclusion criteria and use a 128-slice MDCT with better reproducibility of measurements, we estimate the standard deviation of CAC-progression to be 25%. We consider an absolute difference of 15% in CAC-progression between the two treatment groups a significant effect [33]. To test this difference with a statistical power of 90% (alpha 0.05) we require 59 patients per group. Based on analysis of available data from our center, we estimate a patient drop-out of approximately 35%. This drop-out may have various reasons such as patients requiring coronary artery stenting over the course of the study, occurrence of cardiovascular events such as myocardial infarction requiring percutaneous coronary intervention (PCI) or death, development of exclusion criteria, or subjects no longer willing to participate in the study. Therefore, to obtain sufficient statistical power to demonstrate a possible treatment-effect, we require 90 patients per group for a total number of 180 patients.

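### Patients who adhere poorly or need a vitamin K antagonist can be or must be withdrawn from the study, not only from the tablet, which conflicts with the stated intention-to-treat analysis

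*Protocol article*

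**What the plan says.** - **Analysis (section 2.8).** "Data will be analyzed based on the intention-to-treat principle". GEE is planned for progression over baseline, 12 and 24 months.
- **Withdrawal (section 2.10.5).** The investigator may "withdraw a subject from the study for urgent medical reasons or in case of demonstrable poor adherence to the study medication". This is discretionary. Patients who come to need a vitamin K antagonist have no such latitude: "they will be withdrawn from the study". In both places what ends is participation in the study, not just use of the study medication.
- **Drop-out (section 2.9).** About 35% is expected. The possible reasons include "patients requiring coronary artery stenting over the course of the study", "myocardial infarction requiring percutaneous coronary intervention (PCI) or death, development of exclusion criteria" and unwillingness to continue. No split is given, and poor adherence is not listed.
- **Sample size (section 2.9).** 59 per group give 90% power for a 15-point difference with an SD of 25. This is raised to 90 per group for drop-out.
- **Scans (section 2.5).** A native CT is scheduled at 12 months and a repeat CT including angiography at 24 months. Nothing is said about scanning patients who have been withdrawn.

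**The concern.** Intention-to-treat needs the outcome of each randomised patient regardless of adherence or later treatment. A rule that ends study participation for poor adherence or a new co-medication stops that outcome from being collected. No analysis plan can later restore a 24-month scan that was never taken.

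The expected loss is large, about a third of each arm, and some of the named reasons lie close to the outcome. The article's introduction describes CAC as a strong, independent marker of cardiovascular complications and links its annual change to plaque burden. Patients who need stenting or have an infarction are therefore plausibly faster progressors. If MK-7 slows progression, more of them would come from placebo, and a comparison of those who remain would understate the effect. If loss differs between arms for other reasons, such as adherence, the bias can go either way.

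**Working it through.** **Inputs from section 2.9:** difference 15 points, SD 25, power 90%, drop-out 35%, 59 evaluable and 90 randomised per group. Section 2.8 gives two-sided alpha 0.05.

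**1. The plan's own figure.** n = 2(1.960 + 1.282)² × 25² / 15² = 58.4, so 59 per group. Power at 59 is 90.3% (normal approximation) or 89.8% (noncentral t). For drop-out, 59/0.65 = 90.8, which is 91 rounded up; the stated 90 is close enough. The arithmetic is sound. It also shows what is powered: 90 × 0.65 = 58.5 evaluable patients per group, with 31.5 per group expected to be lost.

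**2. Loss related to progression (illustration).** Assumed: mean annual progression 35% on placebo and 20% on MK-7, SD 25, overall loss 35%, and all loss following a logistic model in the patient's own progression. The log-odds slope is 0.5 or 1.0 per SD, that is odds ratios of e^0.5 = 1.6 and e^1.0 = 2.7. The documents give no slope. Integrating over the normal distribution of progression:

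| | OR 1.6 per SD | OR 2.7 per SD |
|---|---|---|
| Loss, placebo / MK-7 | 38% / 32% | 41% / 29% |
| Evaluable of 90, placebo / MK-7 | 55.6 / 61.4 | 53.4 / 63.6 |
| Completer means | 30.48 / 16.23 | 26.56 / 13.81 |
| Completer difference | 14.25 | 12.75 |
| Completer SDs | 24.3 / 24.4 | 22.9 / 23.2 |
| Power with completer SDs | 88% | 84% |
| Power with SD fixed at 25 | 86% | 78% |

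Power is from the noncentral t. For OR 1.6, SE = √(24.34²/55.59 + 24.40²/61.41) = 4.51 and 14.25/4.51 = 3.16. For OR 2.7, SE = 4.28 and 12.75/4.28 = 2.98. With SD 25 the SEs are 4.63 and 4.64. The last entry is 77.8%, or 77.5% if the difference is taken as 12.7.

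**3. Unequal loss with no true effect (illustration).** If lost patients progress x points faster than completers, the completer mean is too low by loss × x, so the bias in the difference is x times the difference in loss. With x = 20 and loss of 30% against 40%, bias = 20 × 0.10 = 2 points. At 58 per group SE = 25√(2/58) = 4.64, and the two-sided type I error is about 7.2%. With x = 25 and 25% against 45%, bias = 5 points and the error is about 19%. With equal loss and equal selection the bias is 0.

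**4. What the 90% becomes if everyone is followed.** Let patients who would have been lost keep a fraction f of the effect. Difference = 15 × (0.65 + 0.35f); SE = 25√(2/90) = 3.73.

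| f | Difference | Power, 90 per group | n per group for 90% |
|---|---|---|---|
| 0 | 9.75 | 74% | 139 |
| 0.5 | 12.375 | 91% | 86 |
| 1 | 15 | 98% | 59 |

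These assume that every patient is scanned, which is an upper limit: deaths and withdrawn consent cannot be recovered.

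**The case against.** Much can be said for the plan, and most of it limits the point.

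- **Forecasts are not rules.** A reader might infer that stenting, infarction or a new exclusion criterion removes a patient from the study. The text does not say so. Section 2.10.5 has one mandatory removal (vitamin K antagonist use) and one discretionary power (urgent medical reasons, poor adherence). The other events appear only in section 2.9, as possible reasons behind a drop-out forecast.
- **The whole 35% is not outcome-related.** The list is open-ended, includes unwillingness to continue and gives no proportions. The outcome-related share is unknown.
- **Withdrawn patients are not said to leave the analysis.** Nothing in the article limits it to adherent, event-free completers. GEE can use a 12-month scan taken before withdrawal. Handling of missing data is normally left to documents not shown here.
- **Safety data on the triggering event are kept.** One might think that a patient withdrawn after a thrombosis disappears from the safety comparison. The event precedes withdrawal, and section 2.10.2 records all adverse events. Only later events could be missed.
- **The illustrated bias is modest** under the plan's own effect, runs toward no effect, and rests on assumed slopes applied to all of the loss.

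All of this stands. It does not remove the conflict. GEE cannot supply scans taken after withdrawal, or any follow-up score for patients who leave before month 12, and its validity then depends on why they left. This is also not a complaint about absent detail: the article states a withdrawal rule and an analysis principle that do not fit together.

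**Conclusion.** The conflict between sections 2.8 and 2.10.5 is in the text and needs no assumption. As written, poor adherence may end outcome collection and vitamin K antagonist use must end participation, with no scan provided afterwards. It is also clear that the 90% power refers to about 59 evaluable patients of 90 per group.

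That part of the loss relates to coronary progression is a reasonable inference from the reasons listed in section 2.9 and the role the introduction gives to CAC. Its share cannot be derived. The bias is therefore illustrative: a fall from 15 to about 14.25 to 12.75 points, and power of about 88% to 84% (86% to 78% with SD fixed at 25), if all loss follows the assumed slopes. It is none if loss and selection are equal in both arms, and may run in either direction if loss differs for other reasons. The sample size arithmetic is not at fault.

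This should be fixed, because uncollected scans cannot be recovered. The documents do not support a claim that the primary result is invalid.

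**What to change.** Reconcile sections 2.8, 2.9 and 2.10.5.

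1. **Section 2.10.5:** separate stopping study medication from leaving follow-up. Whatever rule applies to the tablet, on which no view is taken here, poor adherence or vitamin K antagonist use should not by itself end follow-up. Keep the native CT for the calcium score at the scheduled 12- and 24-month visits, and the safety follow-up, unless the patient withdraws consent or a scan is medically inadvisable.
2. **Section 2.8:** say that patients are analysed as randomised, using all available CAC data. A set limited to patients with a follow-up score should not be called all randomised patients.
3. **Section 2.9:** say that the 90% power is for evaluable completers, and give the power with all 90 per group followed: about 74%, 91% or 98% if patients who would have been lost keep none, half or all of the effect.

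**Cost:** a small amendment with matching consent wording, and scans already scheduled are kept for some patients who would have left. The real price is dilution by patients off treatment. In the worst case shown, 90 per group fall short of 90% power, and the sponsor should accept that knowingly or revisit the sample size.

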## 3. Concluding Remarks

In conclusion, the VitaK-CAC trial will study the effect of menaquinone-7 supplementation on progression of CAC in a randomized, placebo-controlled trial. We hypothesize that MK-7 supplementation will slow down the progression of CAC in patients with CAD. So far, no treatment options are available for vascular calcification, and this trial may lead to a treatment option for vascular calcification and cardiovascular disease.

The result of this study will be expected at the end of 2017.
